## Study centres and investigator

| Centre No. | Centre                                                                                                                               | Principal Investigator                                                                |
|------------|--------------------------------------------------------------------------------------------------------------------------------------|---------------------------------------------------------------------------------------|
| 1          | Onze Lieve Vrouwe Gasthuis (OLVG)
[name]/
[name]
[name]
Netherlands | [name]
[contact]
Mail: [contact]              |
| 2          | MC Haaglanden
Orthopedic Dept.
[name]
[name]
The Netherlands                                            | [name]
[contact]
Mail: [contact] |
| 3          | Reinier de Graaf Gasthuis (RdGG)
afd. Orthopedie
[name]
[name]
Netherlands                                       | [name]
[contact]
Mail: [contact]                          |
| 4          | Hospital Universitario Mar- Esperança
(IMAS)
Servicio de Anestesiología
[name]
[name]
Spain     | [name]
[contact]
Mail: [contact]                 |
| 5          | St. Olavs Hospital
Ortopedisk avdeling
[name]
[name]
Norway                                         | [name]
[contact]
Mail: [contact]                   |
| 6          | Medical University Vienna
Department of Orthopaedic Surgery
[name]
[name]
Austria                     | [name]
[contact]
Mail: [contact]           |

---

Competitive recruitment of a total of 300 patients and a minimum of 20 patients per clinic will be applied.

**Study timetable**

Estimated date of first subject enrolled

28th February 2009

Estimated date of last subject completed

30th November 2009

**Phase of development**

Post-marketing

**Objectives**

The primary objective of this study is to compare clinical efficacy in total hip replacement patients receiving either blood transfusion with the Sangvia® Blood Management System or no autologous transfusion by assessment of need for allogeneic blood transfusion.

The secondary objectives of the study are....

....to observe and compare clinical efficacy by means of postoperative infection rates, use of postoperative antibiotics, length of hospital stay and health status for patients transfused with Sangvia® blood, no blood and/or allogeneic blood.

....to observe and compare clinical efficacy by means of systemic postoperative haemoglobin levels for patients transfused with Sangvia® blood, no blood or allogeneic blood.

.... to collect details in health care utilisation (medications, in-patient service use, blood management) that would allow a calculation and comparison of cost-consequences applying either alternative in the blood management and from the perspective of the payer

....to observe and compare safety by means of adverse events, highlighting renal failures and events potentially related to transfusion, body temperature and other clinical complications for patients transfused with Sangvia® blood, no blood or allogeneic blood.

**Study design**

The study is an assessor blind, prospective, randomized, controlled, multi-centre investigation of 300 patients.

**Target subject population**

Patients scheduled for either primary or secondary total hip arthroplasty

**Investigational product**

Intra-operative, and if bleeding continues after surgery, possibly also post-operative autologous blood transfusion with the Sangvia® system (test group).

**Comparator**

No autologous blood, i.e. allogeneic blood transfusion when needed (control group).

**Duration of treatment**

Patients will be followed during their hospital stay and at 2 months after discharge.

**Outcome variables****Primary outcome variable:**

- Frequency and amount of allogeneic blood transfusion

**Secondary outcome variable(s):**

- Post-operative infection rate (SIRS reaction, clinical symptoms, wound infection, CRP and LPC)
- Post-operative antibiotic use
- Length of hospital stay
- Post-operative haemoglobin concentration
- Demographical data (e.g. vital signs, age, gender etc)
- Health status questionnaire (i.e. EQ-5D)

**Safety variable(s):**

- Adverse events (AE, SAE, ADE) rated for causality
- Laboratory measurements (Hb, Hct/EVF, TPC, LPC, Na+, K+, CRP, Creatinine and Glomerular Filtration Rate (GFR)/Creatinine Clearance (CCr))

**Health economics variable(s):**

- Units and ml of allogeneic blood transfusions
- Number of post-operative bed days by general and intensive care unit
- Post-operative medications

**Statistical methods**

Descriptive statistics, i.e. mean, median, standard deviation, minimum and maximum values for continuous data and frequencies and percentages for categorical data, will be used together with different statistical tests. Fischer Exact test will be used to test frequencies of dichotomous response variables. The non- parametric Wilcoxon Rank Sum test will be used to test differences in continuous response variables between the parallel treatment groups. Wilcoxon Signed Rank test will be used to test differences over time within each treatment group. P-values equal to or below 0.05 are considered as statistically significant. Subgroup analyses of type (primary and secondary) and complexity (easy < 1 hour, medium 1-2 hours and complex > 2 hours) of surgery are planned.

# LIST OF ABBREVIATIONS AND DEFINITION OF TERMS

The following abbreviations and special terms are used in this study protocol.

| Abbreviation or special term             | Explanation                                                                                                                                                                      |
|------------------------------------------|----------------------------------------------------------------------------------------------------------------------------------------------------------------------------------|
| ADE                                      | Adverse Device Effect (see definition in Section 4.4.1.1)                                                                                                                        |
| AE                                       | Adverse Event (see definition in Section 4.4.1.1)                                                                                                                                |
| C Cr                          | Creatinine Clearance                                                                                                                                                             |
| CRF                                      | Case Report Form                                                                                                                                                                 |
| CRP                                      | C-reactive protein                                                                                                                                                               |
| CSA                                      | Clinical Study Agreement                                                                                                                                                         |
| Ethics Committee                         | Synonymous to Institutional Review Board and Independent Ethics Committee                                                                                                        |
| EVF                                      | Erythrocyte volume fraction, haematocrit                                                                                                                                         |
| GCP                                      | Good Clinical Practice                                                                                                                                                           |
| GFR                                      | Glomerular Filtration Rate                                                                                                                                                       |
| Hb                                       | Haemoglobin                                                                                                                                                                      |
| Hct                                      | Haematocrit, erythrocyte volume fraction,                                                                                                                                        |
| International Co-ordinating investigator | If a study is conducted in several countries the International Co-ordinating Investigator is the Investigator co-ordinating the investigators and/or activities internationally. |
| ISF                                      | Investigator's Study File                                                                                                                                                        |
| K +                           | Potassium                                                                                                                                                                        |
| LPC                                      | Leukocyte Particle Count                                                                                                                                                         |
| Na +                          | Sodium                                                                                                                                                                           |
| OC                                       | Oracle Clinical, the clinical data management system used at Astra Tech for capture and validation of study data                                                                 |
| PRO                                      | Patient Reported Outcome                                                                                                                                                         |
| Principal Investigator                   | A person responsible for the conduct of a clinical study at an investigational study site. Every investigational study site has a principal investigator                         |
| SAE                                      | Serious adverse event (see definition in Section 4.4.1.1)                                                                                                                        |
| SIRS                                     | Systemic Inflammatory Response Syndrome                                                                                                                                          |
| TPC                                      | Thrombocyte Particle Count/Platelets                                                                                                                                             |

# 1 INTRODUCTION

There are risks related to blood incompatibility and blood-borne diseases when using allogeneic transfusion during and after surgery. Several autologous transfusion alternatives exist on the market today and one of them, used for intra- and postoperative blood salvage, is the Sangvia® Blood Salvage System which has been proven safe to use in man. This study is designed to prove clinical benefits/efficacy of the Sangvia® system and to confirm previous reported safety results.

## 1.1 Background

Allogeneic blood transfusions subject patients to risk of infection, allergic reactions, immunosuppression and are also associated with high costs. A variety of alternatives to allogeneic blood transfusions have been proposed, such as the use of solutions to support oxygen transport, human recombinant erythropoietin, intra-operative autologous blood collection, normovolemic hemodilution, preoperative blood salvage and postoperative infusion of shed wound blood. At present autotransfusion is the most commonly used alternative to allogeneic blood transfusions and the application of the autotransfusion techniques has increased along with a reduced need of allogeneic transfusion, reduced costs and minimized exposure to infectious agents. Although autologous blood is proven to be a safe transfusion product it represents only a small percentage of the total amount of blood transfused.

A number of autotransfusion devices are commercially available. The techniques of peri-operative autotransfusion can be subdivided depending on the extent to which the scavenged blood is processed prior to transfusion. In “filtered autotransfusion systems”, the blood is often anticoagulated and filtered, whereas “washed autotransfusion systems” use anticoagulation, cell separation, washing and filtration. Filtered autotransfusion systems collect and transfuse whole blood. Blood is collected from the surgical wound through a suction device or drain and actively aspirated to a reservoir. This reservoir has a macro filter (e.g. 20-150 µm) to remove large particles and cellular debris from the blood. A regulated negative pressure of no more than 150 mmHg is recommended to provide the suction necessary during blood collection. Larger negative pressures are believed to increase haemolysis. If applicable, the aspirated blood is anticoagulated either at the point of collection or in the reservoir. Even without anticoagulation, the blood collected for postoperative autotransfusion does not usually clot as it is defibrinogenated. The blood should be transfused within 6 hours of collection to preserve cellular viability and reduce the risk of infection.

There are several indications for autotransfusion, i.e. orthopaedic surgery, vascular surgery, liver transplantation, trauma and cardiac surgery. Contraindications to blood salvage include infection and malignant disease. The risks of using autotransfusion are mainly related to blood quality and systemic effects on the patient. One example is high free haemoglobin level in salvaged blood due to haemolysis secondary to surgical trauma, suctioning techniques and vacuum aspiration. The systemic levels of free haemoglobin after autotransfusion are however depending on several factors such as amount of retransfused blood, age, sex and medical status of the patient but the clinically critical plasma levels of free haemoglobin have not been determined. Another risk may be related to the potassium concentration in salvaged blood which is dependent on many factors such as degree of cell haemolysis and time elapsed before transfusion. Also, intra-operatively salvaged blood has a low concentration of fibrinogen and of factors V, VIII and X and processing of blood leads to activation of complement and formation of pro-inflammatory cytokines. Postoperatively shed blood has a high concentration of complement anaphylatoxins as well as IL-1, IL-6 and IL-8. High levels of inflammatory mediators may cause the development of circulatory instability and pulmonary insufficiency but may also reduce immunosuppression after surgery and the risk of

postoperative infections. In contrast to the possible risk of autotransfusion there are also possible benefits. E.g. the leukocyte count in salvaged blood is close to that of normal blood, salvaged red cells show normal morphology in contrast to allogeneic donor cells and the concentration of 2,3-diphosphoglycerate is higher in salvaged blood than in banked blood which is associated with higher oxygen delivery capacity. Today, a widespread experience with blood salvage and autotransfusion exists and the reported complications are few. A recommendation for a limit of 1500 ml in intra-operative use and of 2000 ml in postoperative use is considered to be safe.

Clinical efficacy of autologous blood transfusion by means of reduction in allogeneic blood transfusion has been confirmed in the literature for different type of systemse.g. 6,14,40. The Sangvia® Blood Salvage System, a filtered autotransfusion system developed by Astra Tech AB, has however not been specifically investigated with regards to efficacy. The product has been tested in pre-clinical and clinical studies and the quality of intra-operative salvaged blood and the systemic effect after transfusion has been investigated. The results indicate that the blood quality is similar to that of other filtrated system, e.g. postoperative blood salvage with Bellovac® ABT (Astra Tech AB) and that the system is safe to use in man.

## 1.2 Rationale

Transfusion of postoperative autologous blood has been found to reduce the need for allogeneic blood transfusion and also reduce the number of postoperative infections. Publications on the effect of intraoperative filtrated whole blood collection and transfusion are however today very limited or non-existing. The purpose of this study is to document the efficacy, measured by allogeneic blood transfusion rate, of the Sangvia® Blood Management System when used for intra-operative, and if bleeding continues after surgery, possibly also postoperative autologous whole blood transfusion in total hip replacement surgery. The study will also add safety data to previously reported studies.

## 2 STUDY OBJECTIVES

The overall study objective is to investigate efficacy, with regards to allogeneic blood transfusion rate, in total hip replacement patients receiving intra- and possibly also postoperative autologous blood with the Sangvia® Blood Management System compared to patients receiving no autologous transfusion.

### 2.1 Primary objective

The primary objective of this study is to compare clinical efficacy in total hip replacement patients receiving either blood transfusion with the Sangvia® Blood Management System or no autologous transfusion by assessment of need for allogeneic blood transfusion.

### 2.2 Secondary objectives

The secondary objectives of the study are....

....to observe and compare clinical efficacy by means of postoperative infection rates, use of postoperative antibiotics, length of hospital stay and health status for patients transfused with Sangvia® blood, no blood and/or allogeneic blood.

....to observe and compare clinical efficacy by means of systemic postoperative haemoglobin levels for patients transfused with Sangvia® blood, no blood or allogeneic blood.

....to collect details in health care utilisation (medications, in-patient service use, blood management) that would allow a calculation and comparison of cost-consequences applying either alternative in the blood management and from the perspective of the payer

....to observe and compare safety by means of adverse events, highlighting renal failures and events potentially related to transfusion, body temperature and other clinical complications for patients transfused with Sangvia® blood, no blood or allogeneic blood.

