##### **Adverse Event**

An Adverse Event (AE) is any untoward and unintended medical occurrence in a subject. This definition does not imply that there is a relationship between the AE and the medical device under investigation. An AE which is possibly related, is one that may have been caused by the medical device, or treatment, however there is insufficient information to determine the likelihood of this possibility.

- Possibly related: temporal relationship of the onset of the event, relative to the use/administration of the medical device, is reasonable but the event could have been due to another, equally likely cause.
- Non-related (unlikely): temporal relationship of the onset of the event, relative to the use/administration of the medical device, is not reasonable or another cause can itself explain the occurrence of the event.

Ambiguous cases should be considered as possibly related.

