##### **Adverse Device Effect**

An Adverse Device Effect (ADE) is any untoward and unintended response to a medical device. This definition includes any event resulting from insufficiencies or inadequacies in the instructions for use of the medical device or any event that is a result of a user error. This definition also includes treatment- or procedure- related events. ADEs can only occur from the time of medical device use/administration. Here the event is related to the use of the medical device where there is a probable/definite relationship that the event may have been caused by the medical device, or treatment.

- Probably related: temporal relationship of the onset of the event, relative to the use/administration of the medical device, is reasonable and the event is more likely explained by the medical device/treatment than by any other cause.
- Definitely related: temporal relationship of the onset of the event, relative to the use/administration of the medical device, is reasonable and there is no other cause to explain the event.

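### The protocol is inconsistent on what adverse-event causality is rated against, so the objective on transfusion-related events has no like-for-like variable in the two arms

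*Protocol*

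**What the plan says.** The safety objective in section 2.2 is "to observe and compare safety by means of adverse events, highlighting renal failures and events potentially related to transfusion", for patients given Sangvia blood, no blood or allogeneic blood. The synopsis lists the safety variable as "Adverse events (AE, SAE, ADE) rated for causality".

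Section 4.4.1.1 defines the ratings.

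- The general wording is broad: "An AE which is possibly related, is one that may have been caused by the medical device, or treatment".
- The criterion that follows is narrower: "Possibly related: temporal relationship of the onset of the event, relative to the use/administration of the medical device, is reasonable".
- An event is non-related when its timing, "relative to the use/administration of the medical device, is not reasonable or another cause can itself explain the occurrence of the event".
- The ADE definition opens with the device: "An Adverse Device Effect (ADE) is any untoward and unintended response to a medical device". It then widens: "This definition also includes treatment- or procedure- related events". It then restricts the period: "ADEs can only occur from the time of medical device use/administration".
- Probably related is timed from device use but attributed to device or treatment. Definitely related is also timed from device use. Treatment is not defined in this section.

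Section 4.4.1.2 requires all AEs to be logged. For events judged possibly, probably or definitely related to the device, the log must give onset time, action taken, outcome and seriousness. For events judged non-related to the device, it must give a short description and seriousness.

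Section 3.6.1 states that controls have no autologous salvage. Section 6.2 plans Fisher tests of AE proportions between groups, and section 6.3 adds analyses by type of blood received.

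**The concern.** The objective asks about harm from transfusion of either kind. The rating that is collected asks mainly about harm from the device. These are different questions, and they diverge most in the control arm, where the only blood given is bank blood.

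Section 3.2.1 names fewer allogeneic-blood risks among the possible benefits of the system, and lists matching errors and immune reactions among those risks. If reactions to bank blood are filed as non-related, and with less detail, the trial is poorly placed to show that benefit in the terms of its own safety objective. The wording also leaves room for centres to differ: one could treat bank blood as treatment and rate a reaction as related, while another follows the timing criteria and does not.

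The log rule is part of data collection. If an onset time was not required and was not written down, no later analysis plan can supply it.

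**Working it through.** **Wording set side by side**

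| Element | Referent | Reaction to bank blood in a control |
|---|---|---|
| General sentence on possibly related (4.4.1.1) | device or treatment | could qualify |
| Possibly related, timing | device use | no device use to time from |
| Non-related | device timing, or another cause explains the event | fits |
| ADE, opening and extension | device; then treatment or procedure | could qualify |
| ADE, time limit | from device use | excluded if read literally |
| Probably related | timing: device; attribution: device or treatment | the two parts conflict |
| Definitely related | timing: device; no other cause | fails the timing part |
| AE-log rule (4.4.1.2) | relation to the device | less detail required |

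Controls do have a drain (section 3.1). But the AE definition speaks of the device under investigation, and section 3.4.1 identifies that as Sangvia.

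**Two patients traced through the rules**

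1. A control reacts to bank blood. The general sentence could admit it, but each timing criterion needs device use. Read operationally, it is non-related and needs only a description and seriousness.
2. A test patient reacts to bank blood given in addition to Sangvia blood. Timing from device use may be reasonable, but another cause explains the event, so non-related again fits.

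A test patient reacting to salvaged blood is rated related and gets the full record.

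**Who is exposed to bank blood**

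Inputs from section 6.5: 150 per arm, expected allogeneic transfusion 21% in controls and 7% in the test group. The plan's sample size reproduces from the same inputs: (1.96 + 1.2816)² × 4 × 0.14 × 0.86 / (0.07 − 0.21)² = 258.2, against the stated 260. The present point does not depend on it.

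- Controls: 150 × 0.21 = 31.5.
- Test group: 150 × 0.07 = 10.5.
- Share in controls: 31.5 / (31.5 + 10.5) = 75%.

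**How many events might be affected (illustration)**

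The protocol gives no reaction rate. Assume 2% to 20% of patients given bank blood have a reaction.

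- Controls: 31.5 × 0.02 = 0.63 to 31.5 × 0.20 = 6.3.
- Test group: 10.5 × 0.02 = 0.21 to 10.5 × 0.20 = 2.1.
- Total: about 0.8 to 8.4 events.

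**What asymmetry would do to a comparison of related events**

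Suppose the device wording were applied strictly and no control event were rated related. For k events against 0 with 150 per arm, the two-sided Fisher p-value is 2 × C(150, k) / C(300, k). This gives 0.060 for k = 5 and 0.030 for k = 6. Six related events in the test arm would then be nominally significant, whatever number of bank-blood reactions controls had. Section 6.2 does not expressly plan this test.

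**The case against.** The strongest reply has four parts.

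- **The text is not purely about the device.** Treatment appears in the general wording for possibly related, in the ADE definition and in the attribution part of probably related. Ambiguous cases default to possibly related. This stands, and it is why the defect is an inconsistency. A reader might infer that causality is judged against the device alone and that a control's reaction to bank blood is barred from counting as related. The documents do not support that. Section 4.4.1.1 also refers to an appendix for guidance on causality, and neither that guidance nor the CRF is in the text available, so treatment may be clarified there.
- **All AEs are logged and compared.** Section 6.2 tests AE proportions without restricting them to related events, infections are assessed separately, and 6.3 adds analyses by blood type. This stands. The all-AE comparison includes bank-blood reactions in both arms.
- **The objective could be met by selecting event types from the AE log, and that choice can be left to an analysis plan.** This stands for the choice of events. It does not repair the record: without a required onset time, linking a non-related event to the transfusion log depends on what a site chose to write.
- **Serious reactions are followed up through SAE reporting (4.4.1.3).** That is fair, so the loss of detail falls mainly on non-serious reactions.

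**Conclusion.** The point holds as an inconsistency with a practical consequence. Sections 4.4.1.1 and 4.4.1.2 do not agree on the causality referent. On an operational reading, reactions to bank blood tend to be rated non-related in both arms and recorded in less detail. The objective in 2.2 therefore has no like-for-like variable, and any between-arm comparison of related events or ADEs would be asymmetric.

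The number of events is probably small: about 0.8 to 8.4 under the assumed 2% to 20% reaction rate. At the planned rates, 75% of the patients exposed to bank blood are controls. The conclusion assumes that sites follow the timing criteria and the log rule as written, and that no unseen guidance extends treatment to allogeneic blood.

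A reader might go further and infer that the planned safety analysis as a whole is tilted towards showing harm from the device. The documents do not support this. Section 6.2 does not limit its AE test to related events; its reference to total and variable-specific proportions, together with AE, SAE and ADE as safety variables, permits such a test but does not prescribe it.

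**What to change.** 1. Reconcile 4.4.1.1 and 4.4.1.2 so that definitions, timing criteria and log rule use the same referent, and define treatment.
2. Add one item to the AE log for every AE in both arms: potentially related to a blood transfusion: no / autologous / allogeneic / both.
3. Require onset time, action taken and outcome for every event so rated, whatever its relation to the device.
4. In 6.2, name the proportion of patients with at least one such event, compared by randomised arm, as the variable for this objective.
5. Keep the device rating for ADE reporting, without a between-arm test.

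The cost is one CRF field, short edits to 4.4.1.1, 4.4.1.2 and 6.2, and a small extra recording burden per AE. The change has to be in place before data are collected.
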